### Replacement of individual subjects after withdrawal

Inclusion will continue until 554 patients in toto are reached, and patients withdrawing consent will be replaced.

### Follow-up of subjects withdrawn from treatment

No follow-up is different from the normal out-of-study follow-up.

### Premature termination of the study

A decision for premature termination will take place when DSMB analysis shows that preoperative continuation of aspirin causes health dangers for the patient, for example, a significant increase of postoperative hemorrhage leading to reoperation.

## Safety reporting

### Temporary halt for reasons of subject safety

In accordance with section 10, subsection 4, of the WMO, the sponsor will suspend the study if there is sufficient ground that continuation of the study will jeopardize the subject health or safety. The sponsor will notify the accredited METC without undue delay of a temporary halt including the reason for such an action. The study will be suspended pending a further positive decision by the accredited METC. The investigator will take care that all subjects are kept informed.

### Anesthesiological safety assessment

At the request of the METC, a safety assessment of the study protocol by anesthesiologists is performed. In consultation with [name], cardio-anesthesiologist, and the Wetenschapscommissie of the Haga Hospital, no objections were formulated to perform this study. This was supported by the argument that, except for continuing aspirin in the study group, the standard of care is not altered. Recommendation is to announce the initiation of the study in every participating center. This will be done by organizing an informative presentation to the anesthesiology team in every participating center prior to study initiation.

### AEs, SAEs, and SUSARs

#### Adverse events (AEs)

Hemorrhage-related complications such as hemorrhage itself, hemorrhage-related neurological deficits such as paresis, anesthesia and cauda syndrome, anemia, hypotension, and increased infection risk.

Thrombo-embolic complications, i.e., myocardial infarction, increase of symptomatic coronary artery disease, brain stroke, or transient ischemic attack will be reported as well.

#### Serious adverse events (SAEs)

Reoperation in case of cauda- and/or nerve compression caused by hemorrhage leading to neurological deficit. Hemorrhage leads to anemia leading to cardiovascular complications such as hypovolemic shock. These results will be reported in a study report.

#### Suspected unexpected serious adverse reactions (SUSARs)

Not applicable.

### Annual safety report

Will be provided annually to the METC and Wetenschapsbureau HMC containing all AEs, SAEs, and study progression.

### Follow-up of adverse events

All AEs will be followed until they have abated, or until a stable situation has been reached. Depending on the event, follow-up may require additional tests or medical procedures as indicated, and/or referral to the general physician or a medical specialist.

SAEs need to be reported till the end of the study within the Netherlands, as defined in the protocol.

### Data Safety Monitoring Board (DSMB)/Safety Committee

After the inclusion of 100 patients, an assessment of the Data Safety Monitoring Board will be requested for continuation of the study or suggestions for adjustment in the study protocol. In case of direct health safety issues, a direct halt of the study can be decided. The reason to appoint a DSMB is because of the invasive therapy which is needed in case of acute bleeding in the continuation group, which is the study group.

The advice(s) of the DSMB will only be sent to the sponsor of the study. Should the sponsor decide not to fully implement the advice of the DSMB, the sponsor will send the advice to the reviewing METC, including a note to substantiate why (part of) the advice of the DSMB will not be followed.

DSMB will be composed of a neurosurgeon, a hematologist, and an epidemiologist, all external and independent to the Aspin trial. The final appointment will take place after study protocol approval by the METC.

The composition of the Board will be as follows:[name]. [name]; internal medicine with expertise in the field of vascular medicine at the Leids University Medical Center.[name], spinal neurosurgeon at Amsterdam University Medical Center.[name], clinical epidemiologist at the Leids University Medical Center.

### Adjucation commission

An adjucation commission will be assembled and assigned in order to assess the correct classification of complications. The commission will consist of a vascular internist, a cardiologist, and a neurosurgeon.

## Statistical analysis

### Co-primary study parameter(s)

Statistical analysis will be performed using SPSS. The risk of hemorrhagic complications and reduction in thrombo-embolic perioperative events within 30 days after surgery will be compared by calculating the confidence intervals of both groups and noninferiority will be claimed if the complication risk percentage stays below 6.1 percentage points.

In order to compare the effect of predefined risk factors on the primary and secondary outcome (Table 2) a multivariate regression model with an intention to treat analysis will be used.

**Table 2 Tab2:** Predefined risk factors

Age	
Sex	
Type of operation Type of spinal procedure: non-instrumented decompression, fusion procedures, spinal level, degenerative, neoplastic	
Duration of surgery	
Amount of preoperative thrombocytes	
Prescribed aspirin dose (80 or 100 mg)	
Previous cardiac or cerebral infarctions (as well as coronary artery disease and transient ischemic attack)	
Duration of surgery	
Type of spinal surgery	

Additional outcomes will be the hemorrhagic outcome measures (perioperative blood loss, hemorrhage-related complications, need for reoperation, and transfusion requirement) that will be compared among both treatment groups with a chi-square or Student’s *t*-test. The treatment group bleeding risk is assumed to be below 0,0710 under the null hypothesis of inferiority.

Follow-up within the study ends at day 30 after surgery. All events after day 30 will not be registered for the Aspin trial. Incidental findings will be registered as well and assigned to the involved organ system.

In case of missing data, patients of the treating surgeon can be contacted to complete the missing information.

All efforts will be made to assemble data for the primary outcome analysis. In case this data is missing, participants will be excluded from the final analysis.

All patients randomized to one of the study arms will be analyzed according to the intention to treat analysis.

Missing data in baseline characteristics will be imputed using multiple imputation (*n*=10) based on the outcome and relevant baseline covariates using the “Multivariate Imputation by Chained Equations” (MICE) algorithm. Patients with missing primary outcomes will be excluded but every effort will be made to obtain follow-up.

The ACTS scale and PROMIS Global-10 score will be compared between pre- and postoperative assessment and between the study and control groups.

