### Sample size calculation

#### Sample size calculation

Because of the research question, the noninferiority of the continuation of aspirin perioperatively in comparison to discontinuation, a noninferiority setup is chosen. Since hemorrhage risk is the main risk of interest in the intervention groups, the sample size calculation is based on these risk percentages. The thrombo-embolic complications are not expected to be raised in the intervention group, as the aspirin functions as a prevention for these events to occur.

The sample size for a noninferiority approach was estimated as *n*=554, *n*=277 per study arm. This was based on the following hemorrhage risk percentages: 1% for the control group, 3% for the intervention group, and 6.1 percentage points as the non-inferiority margin. Calculations were made in PASS Sample Size Software, setting a non-inferiority trial with binary parameters. Below is a summary statement for the sample size estimation.

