#### Summary statement

The current practice in Dutch hospitals is to discontinue aspirin pre-operatively. Annual complication registration in our regional database shows a 1% bleeding risk after spinal surgery with the current management. The study by Rahman et al. had a postoperative hematoma rate of 8% versus 4%, with a difference of 4% when not on aspirin perioperatively while Soleman et al. had a 2.5% in postoperative hemorrhagic complications when continuing aspirin [15, 16]. The POISE2-trial presents a hemorrhage risk of 4.6% in patients continuing aspirin in overall surgical patients [5]. These numbers were assumed to not be representative as the studies and the outcome parameters were not comparable to the Aspin study and the study population was not equivalent. Our spinal expert opinion in the Haaglanden Medical Center recommends to maintain a percentage of 3% as a more realistic bleeding risk for the study group.

Sample sizes of 277 in group one and 277 in group two achieve 80% power to detect a

Non-inferiority margin difference between the group proportions of 0.0610. The reference group proportion is 0,0100. The treatment group proportion is assumed to be 0.0710 under the null hypothesis of inferiority. The power was computed for the case when the actual treatment group proportion is 0,.0300. The test statistic used is the one-sided Score test (Miettinen and Nurminen). The significance level of the test was targeted at 0.0250.

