## Methods

### Primary study outcome: composite of the following bleeding complications

Neurological deterioration as a result of hemorrhage in the surgical area with cauda and/or nerve root compression.Post-surgical anemia with hemoglobin level lower than 5 mmol/l, requiring transfusion.Subcutaneous hematoma leading to wound leakage and pain higher than NRS=7.Major and/or minor hemorrhage in any other body system according to the definition of the International Society on Thrombosis and Haemostasis bleeding scale.Postoperative hemorrhage leading to a clinical indication for re-operation (c.q. evacuation of hematoma).

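### Thrombo-embolic events are secondary in every outcome list but sit under a co-primary heading in the analysis section, beside a 6.1-point rule that was built for bleeding and does not name its outcome

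*Protocol article*

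**What the plan says.** The Abstract, Objectives and Methods of the protocol article all define the primary outcome as bleeding only ("Primary study outcome: composite of the following bleeding complications"). All three list myocardial infarction, venous thromboembolism, stroke and arterial thromboembolism among the secondary outcomes.

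The sample size section takes the same view: "Since hemorrhage risk is the main risk of interest in the intervention groups, the sample size calculation is based on these risk percentages". The margin appears among those haemorrhage percentages ("6.1 percentage points as the non-inferiority margin"). The section adds that thrombo-embolic complications are not expected to rise under continuation, and it gives no rate or margin for them.

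The Statistical analysis section differs. Its first subsection is headed as co-primary and opens with "The risk of hemorrhagic complications and reduction in thrombo-embolic perioperative events within 30 days after surgery will be compared". The same sentence ends with the only decision rule in the article: "noninferiority will be claimed if the complication risk percentage stays below 6.1 percentage points". It does not say which complication is meant. Later in that subsection the 0.0710 limit is tied to the bleeding risk of the treatment group.

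**The concern.** One endpoint has two incompatible statuses in the same document, and the conflict falls in the section that states the confirmatory analysis.

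- **If the rule covers both outcomes**, a margin derived for bleeding is applied to infarction, stroke and thrombosis. These are the events that continuation is meant to prevent, and the plan itself words the question as a reduction. A non-inferiority margin cannot establish a reduction.
- **If the rule covers bleeding only**, a declared co-primary has no hypothesis, no margin and no decision rule.

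On both readings it is unclear whether the trial succeeds on bleeding alone or needs both outcomes. This matters because the balance of bleeding against thrombosis is the rationale of the trial, so a thrombo-embolic statement is likely in the report. A finding of thrombo-embolic non-inferiority at 6.1 points could look confirmatory while saying little.

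**Working it through.** **Inputs from the protocol** (Sample size calculation and Summary statement): 277 per arm; margin 0.061; one-sided alpha 0.025; Miettinen-Nurminen score test. For bleeding, "The reference group proportion is 0,0100" and "The power was computed for the case when the actual treatment group proportion is 0,.0300", that is 1% and 3%. No thrombo-embolic rate is given for this population, so those below are assumptions, shown as a range.

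**Step 1: reproduce the stated design for bleeding.** Under the null difference of 0.061, the constrained maximum-likelihood proportions are 0.0673 (treatment) and 0.0063 (control).

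- s0 = √(0.0673×0.9327 + 0.0063×0.9937) = 0.2627
- s1 = √(0.03×0.97 + 0.01×0.99) = 0.1975
- n = [(1.960×s0 + 0.8416×s1) / (0.061 − 0.02)]² = [(0.5149 + 0.1662)/0.041]² ≈ 276 per arm

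At 277 per arm, power is 80.2% by this approximation and 81.5% by exact enumeration. The stated 277 and 80% reproduce, so the bleeding design is not in question here.

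**Step 2: apply the same rule to thrombo-embolic events.** For true rates p_T (continuation) and p_C (discontinuation), with X_T and X_C binomial on 277:

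P(declare non-inferiority) = Σ P(X_T = i) P(X_C = j), summed over all (i, j) with score statistic at 0.061 ≤ −1.96.

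| Discontinuation | Continuation | P(non-inferior) |
|---|---|---|
| 1% | 1% | 99.98% |
| 2% | 2% | 99.3% |
| 3% | 3% | 97.0% |
| 5% | 5% | 88.3% |
| 8% | 8% | 73.0% |
| 1% | 2% | 97.7% |
| 2% | 4% | 70.8% |
| 3% | 6% | 37.5% |
| 1% | 5% | 23.3% |

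In counts, the rule passes with 9 events on continuation against 0 on discontinuation (3.2% v 0%). It also passes with 11 against 3 (4.0% v 1.1%).

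**Step 3: power for a reduction.** This uses the same exact enumeration with a zero-difference score test at two-sided 5%, 277 per arm and the rate halved by continuation.

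| From | To | Power |
|---|---|---|
| 1% | 0.5% | about 9% |
| 2% | 1% | about 15% |
| 3% | 1.5% | about 22% |
| 5% | 2.5% | about 34% |

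The usual normal approximation gives 10%, 16%, 22% and 34%, so the choice of method does not matter.

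**The case against.** The strongest reply is that the 6.1-point rule was only ever meant for bleeding. It speaks of one complication risk and names no outcome. The margin is listed with the haemorrhage percentages, and 0.0710 is the 1% bleeding rate plus 0.061. The same analysis section ties that limit to bleeding risk and refers to the primary outcome analysis in the singular. All of this stands. A reader might infer that the plan expressly applies the bleeding margin to thrombo-embolic events. The sentence structure points that way, but the text does not say so. The reply does not rescue the section, however, because on the bleeding-only reading the other outcome under the co-primary heading has no rule.

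Second, a reader might infer that any thrombo-embolic claim would pass almost automatically. The figures do not support that in general. At equal rates of 5% and 8% the pass probability is 88% and 73%, and under marked harm it falls to 37% (3% v 6%) or 23% (1% v 5%). The description fits only low assumed rates, up to about 3% in both arms, or a real benefit.

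Third, a reader might infer that the trial is free to pick its primary endpoint once the data are in. The outcome lists and the bleeding-only sample size, all published, limit that. The heading creates ambiguity, not a free choice.

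Fourth, the Synthesis under Structured risk analysis gives the aim as a reduction or a stable presence of these events, so superiority is not the only possible reading. That is true, but it shows that the thrombo-embolic hypothesis is unsettled. A rule for combining endpoints may also sit in an analysis plan that is not shown. The point does not depend on its absence, since the contradiction is in the text at hand.

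**Conclusion.** The point holds as an internal contradiction about the confirmatory endpoint, together with a decision rule that does not name its outcome. It should be fixed. It does not invalidate the design, because the bleeding sample size reproduces and is unaffected.

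The contradiction needs no assumptions. Its size does, because it depends on the rule covering thrombo-embolic events and on assumed rates. On that reading the margin is uninformative at low rates: at least 97% of trials pass with equal rates up to 3%, and 98% and 71% pass when continuation doubles a rate of 1% or 2%. It discriminates better at higher rates or under larger harm. Separately, the trial has little power for a reduction: between about 9% and 34% for a halving from rates of 1% to 5%.

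**What to change.** In the Statistical analysis section:

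1. Replace the co-primary heading with one that names a single primary study parameter.
2. State that the 6.1-point rule applies to the risk difference in the haemorrhagic composite only.
3. Report thrombo-embolic events as secondary, with a risk difference and 95% score interval, without a margin or a confirmatory claim, and say that the trial is not powered to show a reduction.

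This agrees with the outcome lists and the sample size basis. It costs wording only and changes neither the number of patients nor the data collected.

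If the sponsor does intend co-primary status, the outcome lists must be changed to match. Thrombo-embolic events then need their own hypothesis (reduction or non-inferiority), an assumed rate, a margin or superiority test, and a rule for combining the two outcomes. That route is more than wording: the sample size would have to be reworked, and for a reduction 277 per arm falls well short over the rates shown.

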### Synthesis

Aspirin is a medication, which is widely used. In situations of emergency surgeries, experience is available where surgeries are performed without discontinuation of aspirin. In case of hemorrhage-related indication, a thrombocyte transfusion can take place, where this is not the standard of care. This gives a point of view about the need to discontinue aspirin in elective low-complex lumbar surgeries. On the other hand, one of the goals of this study is to provide evidence for the reduction or a stable presence of cardiovascular and/or neurological thromboembolic events with no increase in risk present of hemorrhage-related complications. Concerning the overall risk of life-threatening or irreversible complications in the study populations, there is no rationale to support an increase in that risk.

The remaining risks of complications in the study groups are acceptable, because the complications are known risks and manageable complications with therapies that are standard of care in current protocols. This together with the profit of the reduction of thromboembolic events as mentioned earlier.

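### The written non-inferiority rule does not match the test behind the sample size: it names no between-arm difference, upper limit or confidence level, and its type I error runs from about 0.5% to 47% by reading

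*Protocol article*

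**What the plan says.** **Design (Protocol article, Sample size calculation and Summary statement).** The planning values are "1% for the control group, 3% for the intervention group, and 6.1 percentage points as the non-inferiority margin". The Summary statement places the 0.0610 margin on the difference between the group proportions. It gives the null value for the treatment arm: "The treatment group proportion is assumed to be 0.0710 under the null hypothesis of inferiority". It also names the test ("The test statistic used is the one-sided Score test (Miettinen and Nurminen") and its level: "The significance level of the test was targeted at 0.0250".

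**Analysis (Protocol article, Statistical analysis, Co-primary study parameter(s)).** Haemorrhagic complications and the reduction in thrombo-embolic events within 30 days are to be compared by calculating a confidence interval for each group, and "noninferiority will be claimed if the complication risk percentage stays below 6.1 percentage points". Further down, the same section restates the hypothesis: "The treatment group bleeding risk is assumed to be below 0,0710 under the null hypothesis of inferiority".

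**The concern.** The sentence that decides the trial should be the test for which the trial was sized. Here it is not recognisably so.

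- It compares a complication risk percentage, with no arm named, against 6.1. In the design, 6.1 points is the margin on the difference. The corresponding boundary for the continuation arm alone is 7.1%.
- It mentions an interval per arm. It does not say that an upper confidence limit must lie below the margin, or at what level.
- It puts thrombo-embolic events in the same sentence, so it is unclear which outcome the claim covers.
- It describes the null of inferiority as a treatment risk below 0.0710. The Summary statement has the risk at 0.0710 under that null, and values below it favour non-inferiority.

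At stake is control of the false-claim rate. Patients and surgeons are not blinded, and a rule open to several readings leaves the choice among them to be made after the data are seen.

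**Working it through.** **Inputs.** All come from Sample size calculation and Summary statement: n = 277 per arm; control risk 0.01; continuation risk 0.03 under the alternative; margin 0.061 on the difference; one-sided alpha 0.025; power 80%. The boundary risk for continuation is 0.010 + 0.061 = 0.071.

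**Step 1: reproduce the stated sample size.** Use the score-test formula with rates restricted to a difference of 0.061. For planning risks of 3% and 1% the restricted rates are 0.0673 and 0.0063.

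- Null standard deviation term: √(0.0673×0.9327 + 0.0063×0.9937) = √0.0690 = 0.2627.
- Alternative term: √(0.03×0.97 + 0.01×0.99) = √0.0390 = 0.1975.
- n = [(1.960×0.2627 + 0.8416×0.1975) / (0.061 − 0.020)]² = (0.681/0.041)² ≈ 276 per arm.

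The protocol states 277, at which the formula gives 80.2% power. Exact binomial enumeration of the Miettinen-Nurminen test gives 81.5%. The design is therefore reproduced as a test of the *difference*.

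**Step 2: turn each reading of the written rule into event counts.** Let X be events among 277 in the continuation arm and Y events among 277 in the control arm.

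- (a) Upper 95% limit of the continuation arm's own risk below 6.1%: X ≤ 9 with the exact or Wilson limit, X ≤ 10 with the Wald limit.
- (b) Upper limit of the two-sided 95% Miettinen-Nurminen interval for the difference below 6.1 points: the planned test.
- (c) Observed continuation risk below 6.1%: 0.061×277 = 16.9, so X ≤ 16.
- (d) Observed difference below 6.1 points: X − Y ≤ 16.

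**Step 3: type I error at 7.1% v 1%, and power at 3% v 1%.** These are exact binomial sums: P(X ≤ k) for (a) and (c), and enumeration over both arms for (b) and (d).

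| Reading | Type I error | Power |
|---|---|---|
| (a) upper limit, continuation arm alone | 0.5% (exact, Wilson) to 1.1% (Wald) | 68% to 79% |
| (b) upper limit of the difference, as planned | 2.05% | 81.5% |
| (c) observed continuation risk | 23.4% | 99.5% |
| (d) observed difference | 47.4% | not needed here |

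**Step 4: dependence on the control risk.** Reading (c) ignores the control arm, so its error moves with the true control risk. With continuation set at control + 6.1 points, P(X ≤ 16) is 34.4% at a control risk of 0.5%, 23.4% at 1%, 9.1% at 2% and 2.9% at 3%.

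**Step 5: two illustrations.**

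- Counts of 16 v 3 (5.8% v 1.1%, difference 13/277 = 4.7 points) pass under (c) and (d). The 95% Miettinen-Nurminen interval is 1.85 to 8.22 points, so the planned test fails.
- In the other direction, if both arms truly had a 5% risk, reading (a) with X ≤ 9 would succeed only 11% of the time, against 88% for the planned test.

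**The case against.** The strongest reply is that the intended test can be recovered. The Summary statement fixes the scale, the test and the level. The analysis sentence itself speaks of percentage points, the unit of a difference, and mentions confidence intervals, which suggests that sampling error was meant to count. Interval method and level are often left to an analysis plan, which is not shown here. The null sentence looks like a drafting slip, since the Summary statement has it right and no computation uses the other wording.

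Much of this stands. A reader might infer that the protocol prescribes an absolute-risk test with no allowance for sampling error, and that its type I error is therefore 23-47%. The document does not support that. The two figures belong to different rules: 23.4% to the observed continuation risk at a 1% control risk, and 47.4% to the observed difference. Both require the intervals in the same sentence to play no part. If the continuation arm's upper limit is used, the rule is conservative and the loss is in power.

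What does not stand is the appeal to a later analysis plan. The protocol does not leave the rule open: it states one, and an analysis plan that followed the sample size section would have to depart from that sentence.

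**Conclusion.** The point holds as a conflict between the stated claim rule and the design. As written, the rule cannot be applied without choosing a reading. At 277 per arm and 7.1% v 1%, that choice moves the type I error from about 0.5% to 47.4%, around a planned value of 2.05%. The low end costs power: 68-79% against 81.5%.

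The figures assume independent binomial outcomes, 277 analysed per arm, a 1% control risk except where varied above, and 95% two-sided limits in the interval readings, since the analysis section states no level. The misstated null is a minor wording error that should be corrected at the same time. It adds nothing to the size of the problem. Because this one sentence decides the trial, it should be corrected before the data are analysed.

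**What to change.** Replace the claim sentence in Co-primary study parameter(s) with: *Non-inferiority is claimed if the upper limit of the two-sided 95% Miettinen-Nurminen confidence interval for the risk difference (continuation minus discontinuation) in the haemorrhagic composite is below 6.1 percentage points.* This restores the planned properties (type I error 2.05%, power 81.5%).

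In the same edit:

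- State that thrombo-embolic events are compared separately, as secondary outcomes, and are not part of this claim. The article's outcome lists already class them as secondary.
- Correct the null to a treatment risk of at least 0.0710 at a 1% reference risk, that is, a difference of at least 6.1 points.
- Point the sentence to one definition of the composite. The Abstract and Objectives list four components, and Methods adds a fifth (haemorrhage with an indication for re-operation).

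The cost is a wording amendment, with no new patients or data. The one practical downside is that the interval may need a macro or software other than default SPSS.

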### Inclusion criteria

In order to be eligible to participate in this study, a subject must meet all of the following criteria:Scheduled low complex lumbar spinal surgery defined as removal of intervertebral disc herniation, decompression of lumbar canal, and/or foraminal stenosis.Preoperative use of aspirinAge >18

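### The risk-factor regression sets seven Table 2 factors against about 11 expected primary events, includes a post-randomisation covariate and lists a category that the exclusions leave empty

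*Protocol article*

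**What the plan says.** The section Co-primary study parameter(s) of the protocol article describes two separate analyses. Non-inferiority is judged from confidence intervals against 6.1 percentage points. A further sentence then introduces the regression: "In order to compare the effect of predefined risk factors on the primary and secondary outcome (Table 2) a multivariate regression model", to be run by intention to treat.

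Table 2 supplies the factors in nine rows. The row "Duration of surgery" appears twice. Type of surgery appears once with its categories, "Type of spinal procedure: non-instrumented decompression, fusion procedures, spinal level, degenerative, neoplastic", and again in the last row. That leaves seven distinct factors: age, sex, type of procedure, duration, platelet count, aspirin dose and vascular history. Treatment arm is not in the table.

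Other sections bear on this list:

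- Inclusion criteria limit surgery to "removal of intervertebral disc herniation, decompression of lumbar canal, and/or foraminal stenosis". Exclusion criteria remove spinal oncology.
- Use of co-intervention and Escape medication mention lumbar fusion, but only as a possible later extension.
- Study procedures places randomisation at the time the operation is scheduled.
- Sample size calculation gives the planning rates: "1% for the control group, 3% for the intervention group, and 6.1 percentage points as the non-inferiority margin", with 277 patients per arm.

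**The concern.** A regression for a binary outcome is limited by its number of events, not its number of patients. With rates of 1% and 3%, 554 patients give few events, and the list of factors looks long for them. The model is also meant for the secondary outcomes, which include each component of the composite; none of these can have more events than the composite.

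Two features of the list add to this. Duration of surgery is observed after allocation and may be lengthened by bleeding, so it may lie on the path from continued aspirin to the outcome. Some procedure categories do not match the eligible population.

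At stake is the reliability of the risk-factor estimates for rare outcomes, and of any adjusted treatment effect that might be printed beside the main result.

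**Working it through.** **Plan's own figure first.** Inputs from Sample size calculation and Summary statement: 1% and 3%, margin 0.061, one-sided alpha 0.025, power 80%, score test. The proportions restricted to a difference of 0.061 are 0.0673 and 0.0063.

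- s0 = √(0.0673×0.9327 + 0.0063×0.9937) = 0.2627
- s1 = √(0.03×0.97 + 0.01×0.99) = 0.1975
- n = ((1.960×0.2627 + 0.842×0.1975)/(0.061 − 0.020))² ≈ 276 per arm

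The stated 277 is reproduced within rounding; exact power at 277 is 81.5%.

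**Expected primary events.** 277×0.01 + 277×0.03 = 2.77 + 8.31 = 11.08. The 95% range over repeated trials is 5 to 18.

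**Events per factor.** Nine rows minus two repeats gives seven factors. 11.08/7 = 1.6; with treatment added, 11.08/8 = 1.4. One parameter per factor is generous, because the procedure row names several categories.

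**Sensitivity to the rates.**

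| Rates in the two arms | Events | Per 7 | Per 8 |
|---|---|---|---|
| 1% and 1% | 5.5 | 0.8 | 0.7 |
| 1% and 3% (planned) | 11.1 | 1.6 | 1.4 |
| 1% and 7.1% (null) | 22.4 | 3.2 | 2.8 |
| 4% and 8% (craniotomy study cited in Summary statement) | 33.2 | 4.7 | 4.2 |

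The ratio stays below 5 throughout. The protocol itself regards the last pair as not representative.

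**Precision.** Take one binary factor held by half the patients (an assumed prevalence) and unrelated to bleeding. The events split 5.54 and 5.54 among 277 and 277 patients. SE(log OR) = √(2/5.54 + 2/271.46) = 0.607, so the 95% interval spans a factor of exp(1.96×0.607) = 3.3 each way, about 0.30 to 3.3. This is before six other factors are added.

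**Fitting failures.** P(no control-arm events) = 0.99^277 = 0.062. That alone makes the treatment odds ratio infinite, even with no covariates. Three simulations at the planning rates, with treatment plus seven null covariates (distributions assumed), found separation or non-convergence in 8.1% and 9.8% of 1,500 trials each and in 11.2% of 2,000. In the second, a treatment-only model failed in 5.5%. The covariates therefore add about 8.1 − 6.2 = 1.9 points, 9.8 − 5.5 = 4.3 points and 11.2 − 6.2 = 5.0 points; the empty control arm accounts for most of each total.

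**Duration.** Randomisation precedes surgery, so duration cannot be a baseline variable. The outcome descriptions say that excessive bleeding during surgery can compromise the decompression, so an effect of bleeding on how the operation proceeds is within the protocol's own reasoning. No calculation here measures the resulting bias; the simulated covariates were unrelated to treatment and outcome.

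**Categories.** Neoplastic contradicts the oncology exclusion. Fusion lies outside the current inclusion criteria and would be filled only by the conditional extension.

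**The case against.** The strongest reply is that this regression is not the non-inferiority analysis. Its stated purpose is to examine risk factors, Table 2 omits treatment, and nothing says that an adjusted treatment effect will be reported. In a pure risk-factor model, duration of surgery is a legitimate predictor of bleeding. This stands, and it limits the point. A reader might infer that the regression tilts the trial toward declaring non-inferiority. The document does not support that: the claim rests on confidence intervals, treatment enters the model only by inference from the intention-to-treat wording, and the direction of any bias from duration is plausible but not computed.

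A reader might also take the simulated failure rates as showing that the covariates break the model. They do not: most failures come from an empty control arm, and roughly nine in ten fits converged. Nor is fusion impossible, since two sections foresee an extension; an unused level would simply drop out of the fit.

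Finally, the article does not fix the link function, coding, variable selection or penalisation, and an analysis plan not shown may do so. That is fair, and their absence is no fault. But the article does fix the list of factors and the outcomes to which it applies, and the mismatch with the expected events follows from those alone.

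**Conclusion.** The point holds for a secondary analysis. At the planning rates, seven factors face about 11 primary events: 1.6 per factor, 1.4 with treatment, and no more for any single component. Estimates for these outcomes would be overfitted and imprecise. The count assumes the protocol's own rates and one parameter per factor; across the rates shown it never reaches 5 per factor.

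The statement on duration is conditional: if treatment is in the model, the adjusted effect is not the total effect and could be biased, plausibly toward no difference. The neoplastic level is empty, and fusion is empty unless the extension is adopted. The main non-inferiority comparison, the sample size and the analysis of continuous blood loss are untouched by the shortage of events.

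**What to change.** - Remove duration of surgery from any model used to estimate the treatment effect.
- In Table 2, delete the duplicate rows and the neoplastic level, and keep fusion only if the extension is adopted.
- For the primary composite and other rare binary outcomes, specify a Firth-penalised logistic model with treatment and at most one or two baseline factors, named before data are seen and labelled supportive. The shorter list addresses overfitting; the penalty keeps estimates finite if the control arm has no events, which a shorter list alone would not do.
- Keep the full baseline list for operative blood loss, where every patient contributes information.

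This is a change of wording only, with no new data or patients. Its cost is fewer risk-factor estimates for rare outcomes.
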